### Recruitment and randomisation

A trained RA will be situated in the Centre communal waiting room during recruitment. The RA will approach all clients entering the Centre, ascertain eligibility, and seek written consent. A two-stage consent process will be used. First, the RA will inform clients that the study aims to expand the services provided by the Centre and involves completing a health survey on a touch screen computer and that their case-worker may discuss health issues with them. When they complete the survey, if they reported to smoke, they will be informed, on-screen, that a study for smokers is being conducted and that the RA will seek their consent to participate in the smoking study. They will be told that participation in the smoking study will involve their counsellor or case worker possibly discussing quitting with them, and that they will be asked to return to the Centre in one, six and 12 months time to complete the survey and conduct a breath test for carbon monoxide (CO) measurement. Consenting clients will be assisted in the use of the touch screen survey. The RA will review the clients' smoking status on a touch screen survey print-out and randomly allocate participants who are current smokers to the control or intervention group depending on whether it is an intervention or control week. Intervention or control times will be randomly allocated in blocks of four by a computer generated randomisation procedure. Clients who are not smokers will not participate further in the study.

### Touch screen computer baseline survey and print-outs

Studies indicate that touch screen computers are a confidential, acceptable, feasible, user-preferred, and cost-effective mechanism for collecting health information in vulnerable populations [32-37]. The computer will be placed in a private location ensuring confidentiality. The RA will be present at all times when the computer is in use. An additional advantage of the computerised data collection is that it can provide 'real time' results, immediately available to users and staff [33]. The computer will provide intervention participants with two print-outs of their results with a checklist that will outline components of the intervention their case worker should address. One copy will go to the case worker and one will be retained by the client. Clients and staff will be asked to keep checklists and mark off the components of the intervention 1) offered, 2) accepted or refused by the client, and 3) provided. These print-outs will form one component of the intervention as well as process measures.

### Definition of current smoker

The survey will assess demographic characteristics, client smoking status as well as a number of screening tools (such as nicotine dependence, partner's smoking status, depression, financial stress). Self-reported smoking will be determined using the following questions "Which of the following best describes your smoking status?" and respond by selecting from "I'm a smoker, I smoke daily", "I'm a smoker, I smoke occasionally", "I'm an ex-smoker, I never smoke now" or "I'm a non-smoker, I have never smoked." *Clients who smoke daily or occasionally will be asked if they have smoked in the past 7 days and those who have will meet the definition of current smokers for the purpose of this trial. *The use of these items to elicit smoking history has demonstrated accuracy in past research [38].

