### Sample size

A sample of 200 participants per group at 12 months will allow detection of a difference in smoking cessation rates of 8% between groups at 12 months (slightly smaller difference of 7% can be detected at 1 month), based on 5% smoking cessation in the usual care group and 13% in the intervention group, at 5% significance level and 80% power. This effect size is achievable and important from a population-effect perspective. Non-randomised and observational studies using less intensive smoking cessation interventions within disadvantaged groups have demonstrated high cessation rates [25,28-30]. Estimating that 30% of the sample are lost to follow-up (10% at each of one, six and 12 months), 290 patients per group will be recruited at baseline. The Centre receives approximately 50 new clients a week and 50% of those are for ongoing counselling care. All new clients will be eligible to complete the baseline touch screen computer survey. Over a 12-month recruitment period, 1,300 new clients will attend for counselling services. Staff estimate that 60%-90% of clients are current smokers. Assuming a median value of 75%, there will be approximately 975 eligible clients during the study period. Assuming a consent rate of 60% [28-31], 585 individuals will consent to participate in the study.

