### Measures

#### Primary outcome measure - *client validated self-reported smoking cessation*

There will be two primary outcome measures obtained at one, six and 12 month follow-up: 1) 24-hour CO validated self-reported smoking cessation and 2) 7-day self-reported smoking cessation. These follow-up time periods and measures of smoking cessation have been recommended by the Society for Research on Nicotine and Tobacco (SRNT) workgroup [42] for measuring smoking cessation. Seven-day smoking cessation will be defined as abstinent for the past seven days at one, six and 12 months respectively. Seven-day point prevalence abstinence is a common and recommended cessation outcome and has the highest concurrent validity of a range of cessation measures [43]. ***Biochemical *v*erification of self-report: ***General population reports and some clinical trial based studies show that misreporting tends to be low, around 5% [38]. Little is known regarding the misreporting rate of smoking status in this population. Thus, this study will use biochemical validation methods to ensure self-report estimates are validated. Verification will be conducted using measures of CO in expired air as recommended by the SRNT Biochemical Verification workgroup [44]. Although cotinine measures provide the gold standard tool for assessing smoking status self-report, the collection of blood, urine or saliva samples with clients in a non-health setting is invasive and impractical. To assess 24-hour smoking cessation, clients will be asked how long ago they last smoked a cigarette, cigar or pipe? (and respond by indicating, last four hours, between 4-8 hours ago, between 8-24 hours ago, more than 24 hours ago). Twenty four-hours is the recommended biochemically verifiable window for CO in expired air [44]. The Jarvis protocol will be used to record expired air CO. A cut-off point of 8 ppm will be used to define a smoker [44]. Measuring CO in expired air has demonstrated high sensitivity and specificity of around 90% for both [44].

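### The 24-hour CO-validated primary outcome can score an occasional smoker with unchanged habits as a quitter, because entry requires only some smoking in the past 7 days

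*Protocol article*

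**What the plan says.** All references are to the protocol article.

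**Entry (Definition of current smoker).** One of the smoking-status options is "I smoke occasionally". Those reporting that they "smoke daily or occasionally will be asked if they have smoked in the past 7 days and those who have will meet the definition" for inclusion. No minimum frequency is set, and smoking in the last 24 hours is not required.

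**Outcome (Primary outcome measure).** The two primary outcomes, at one, six and 12 months, are "24-hour CO validated self-reported smoking cessation and 2) 7-day self-reported smoking cessation". For the first: "To assess 24-hour smoking cessation, clients will be asked how long ago they last smoked a cigarette, cigar or pipe". After the most recent category, the response options are "between 4-8 hours ago, between 8-24 hours ago, more than 24 hours ago", and only the last of these is compatible with 24-hour abstinence. For the breath test: "A cut-off point of 8 ppm will be used to define a smoker". The same section gives 24 hours as the period that expired CO can verify.

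**Analysis (Efficacy of intervention).** Each primary outcome is compared by chi-square. Occasional smokers are not excluded, stratified or analysed separately.

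**Sample size.** The target of 200 per group at 12 months is "based on 5% smoking cessation in the usual care group and 13% in the intervention group", at 5% significance and 80% power. The section does not say which of the two primary outcomes these rates describe.

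**The concern.** A cessation outcome should require a change from the state that made the person eligible. Here the look-back is seven days at entry and one day at follow-up. Anyone whose usual gap between cigarettes exceeds a day can fall between the two. CO cannot be expected to expose such a person, because the self-report being verified is true: they did not smoke in the last 24 hours.

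Two things are at stake. The first is interpretation: a headline validated cessation rate would mix people who quit with people who smoke as before. The second is power: participants who pass in either arm without changing raise both rates and shrink the difference, and the sample size has no slack to absorb this.

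**Working it through.** **1. Do the definitions overlap?** Take a client who smokes occasionally and last smoked three days ago.

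- Entry: smoked within 7 days, so eligible.
- 24-hour outcome: last smoke over 24 hours earlier, and CO expected to be below 8 ppm, so abstinent.
- 7-day outcome: smoked within 7 days, so not abstinent.

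The same holds for any last smoke about 2 to 6 days before the visit. The 24-hour outcome overlaps the entry definition. The 7-day outcome is its complement, so nobody can meet it at enrolment.

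**2. Reproduce the plan's figure.** Inputs from Sample size: 5% v 13%, 5% significance, 200 per group. Sidedness is not stated, so two-sided is assumed. With no continuity correction,

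power = Φ[(d − 1.96 × SE0) / SE1], where SE0 = √(2 p̄(1 − p̄)/200) and SE1 = √((pC(1 − pC) + pI(1 − pI))/200).

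With pC = 0.05, pI = 0.13, p̄ = 0.09 and d = 0.08: SE0 = 0.02862 and SE1 = 0.02834. Power = Φ[(0.08 − 0.05609)/0.02834] = Φ(0.844) = 80.1%. The matching sample-size formula gives exactly 200 per group, so the plan's figure is reproduced.

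**3. Add unchanged occasional smokers.** Neither input below is in the documents; both are assumed and varied.

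- s = share of participants who smoke occasionally
- q = chance that such a person, with habits unchanged, is over 24 hours from the last cigarette at a visit
- b = s × q = share of participants who pass without any change

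Apply the plan's rates to everyone else:

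- control: pC = b + (1 − b) × 0.05
- intervention: pI = b + (1 − b) × 0.13
- difference: (1 − b) × 0.08

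Example with s = 10% and q = 50%: b = 0.05, pC = 0.0975, pI = 0.1735, d = 0.076. Then SE0 = 0.03423 and SE1 = 0.03401, so power = Φ[(0.076 − 0.06708)/0.03401] = Φ(0.262) = 60%.

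Power at 200 per group:

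| Share s | q = 20% | q = 30% | q = 50% | Control rate at q = 50% |
|---|---|---|---|---|
| 1% | 79% | 79% | 78% | 5.5% |
| 2% | 78% | 77% | 76% | 6.0% |
| 5% | 76% | 74% | 70% | 7.4% |
| 10% | 72% | 68% | 60% | 9.75% |
| 20% | 64% | 57% | 46% | 14.5% |

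**4. Does the form of the model matter?** Two alternatives set the control rate at (1 − s) × 0.05 + s × q, with q = 50%. If the full 8-point difference is kept, power is 72%, 65% and 55% at shares of 5%, 10% and 20%. If occasional smokers contribute no treatment effect, so that the difference is (1 − s) × 8 points, power is 68%, 57% and 40%. The direction is the same throughout; the size depends on inputs that the documents do not give.

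**The case against.** The case against has real force, and most of it limits how far the point can go.

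- **A reader might infer that the 5% control rate is wrong.** The documents do not support that. Sample size does not tie 5% v 13% to either outcome. If the rates belong to the 7-day outcome, or already include occasional smokers who pass, the stated 200 per group and 80% stand.
- **A reader might infer bias in favour of the intervention.** Under random allocation, unchanged occasional smokers are expected in both arms. The effect on the comparison is dilution, which is conservative. The absolute rates are still inflated.
- **A reader might infer that clients would be recorded as quitters on the day they enrol.** The overlap lies in the definitions. CO testing is described only for the one, six and 12 month visits.
- **The plan has partial safeguards.** The other primary outcome, 7-day abstinence, cannot be met at enrolment, and continuous abstinence at six and 12 months is secondary. Both would be read beside the 24-hour rate. But the 7-day outcome is defined by self-report. The analysis section mentions CO validation in its opening words, yet attaches it only to the 24-hour proportion.
- **Adjustment is planned.** Logistic regression will include baseline variables, which may recover some precision. It does not change who is counted as a quitter.
- **The 24-hour window has a reason.** It is the period CO can verify. That stands, and any longer window rests partly on self-report.
- **The power loss may be small.** At a 1% share it is one to two points.

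**Conclusion.** The point holds as a mismatch between the entry definition and the validated primary outcome. It follows from the document's own wording and needs no outside figure: an occasional smoker with unchanged habits can be counted as a CO-validated quitter at follow-up, and the analysis does nothing to prevent it.

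Its numerical size is conditional. Against 80.1% as designed, power at 200 per group is 79% at the mild end (1% share, 20% chance) and 46% at the severe end (20% share, 50% chance). These figures assume that 5% v 13% applies to everyone other than the unchanged passers and does not already allow for them. They also take participants as independent, as the two-proportion formula that reproduces the plan's 200 does.

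The change should be made because it costs little and because the affected outcome is the one labelled as validated, even though the actual loss may prove minor.

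**What to change.** 1. Make the validated primary outcome 7-day self-reported abstinence plus expired CO below the cut-off. It requires the absence of the very behaviour that defined eligibility, so no client meets it at enrolment.
2. State in Sample size that 5% v 13% refers to this outcome. If those rates were meant for a different outcome, revisit them.
3. Keep 24-hour CO-validated abstinence as a secondary outcome, reported separately for baseline daily and occasional smokers.

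**Cost.** The change is to wording only: the 7-day self-report, the CO reading and baseline daily or occasional status are already collected. There are three downsides. Quit rates will look lower than with a 24-hour window. CO verifies only the last 24 hours, so days 2 to 7 rest on self-report. A very infrequent smoker could still pass at a later visit, so the result should be read alongside continuous abstinence.

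A narrower alternative is to record at baseline whether the client smoked in the last 24 hours and to stratify or adjust for it. That would help the comparison between arms but would leave unchanged smokers in the headline rate.

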### Experimental groups

#### The minimal ethical care (control) group

Consenting, smoking clients who complete the survey during control weeks will receive on-screen information at completion of the survey including advice to quit and the telephone smoking cessation assistance Quitline number.

#### The smoking cessation (intervention) group

will receive an intensive client-centred smoking cessation intervention offered by the caseworker over one to two face-to-face and two telephone contacts.

### Intervention

The theoretical framework for the intervention is based on the PRIME theory of motivation [39]. A number of factors are likely to influence an individual's motivation to smoke and quit [7-17,25]. The theory suggests that in order to motivate change, an intervention must minimise the strength and frequency of the need to smoke, maximise the countervailing desire to remain abstinent, optimise use of medication and maximise the capacity to exercise self control. The intervention aims to: use motivational interviewing [40] to encourage repeated quit attempts among all smokers, maximise use of effective quitting assistance strategies [18] and provide support for life 'stresses' believed to contribute to the high rates of relapse in disadvantaged populations [9-11].

Tailoring will be used as cessation research with disadvantaged groups suggests that in order for the client group to benefit, the intervention must fit their level of need, their unique circumstances and be accessible [22,25,39,41]. Data from the baseline screening survey regarding nicotine dependence, previous quit attempts, depression, partner smoking status, and financial stress will be used to produce an individualised checklist of the types of assistance each client may need.

Other behavioural elements of the intervention program will include use of motivational interviewing, behavioural contracting, provision of pharmacotherapy subsidies, allocation of a support person and support pack, referral to specialist quit services as well as Centre-run Life Skills courses, and follow-up using unscheduled drop-in or phone-in sessions.

#### The Case Worker Sessions

The intervention will be implemented over one or two face-to-face visits (each two weeks apart) which will commence immediately following baseline survey completion, followed by at least two phone contacts (one week apart). This intervention will constitute an add-on to clients' usual regular counselling visits, reducing additional costs to the Centre and to clients. If a client requires further contact, staff will provide further quitting assistance and record what they delivered on their checklist. Clients who do not return within the two week timeframe will be contacted by the caseworker by telephone. Appendix 1 provides a session by session description of the intervention.

#### Staff training and resources

Centre staff will be provided with training in the smoking cessation strategies. Local training will be provided during a one day course. Similar courses are regularly provided for various health professionals. The course will be tailored to the needs of community service staff and clients.

### Measures

#### Primary outcome measure - *client validated self-reported smoking cessation*

There will be two primary outcome measures obtained at one, six and 12 month follow-up: 1) 24-hour CO validated self-reported smoking cessation and 2) 7-day self-reported smoking cessation. These follow-up time periods and measures of smoking cessation have been recommended by the Society for Research on Nicotine and Tobacco (SRNT) workgroup [42] for measuring smoking cessation. Seven-day smoking cessation will be defined as abstinent for the past seven days at one, six and 12 months respectively. Seven-day point prevalence abstinence is a common and recommended cessation outcome and has the highest concurrent validity of a range of cessation measures [43]. ***Biochemical *v*erification of self-report: ***General population reports and some clinical trial based studies show that misreporting tends to be low, around 5% [38]. Little is known regarding the misreporting rate of smoking status in this population. Thus, this study will use biochemical validation methods to ensure self-report estimates are validated. Verification will be conducted using measures of CO in expired air as recommended by the SRNT Biochemical Verification workgroup [44]. Although cotinine measures provide the gold standard tool for assessing smoking status self-report, the collection of blood, urine or saliva samples with clients in a non-health setting is invasive and impractical. To assess 24-hour smoking cessation, clients will be asked how long ago they last smoked a cigarette, cigar or pipe? (and respond by indicating, last four hours, between 4-8 hours ago, between 8-24 hours ago, more than 24 hours ago). Twenty four-hours is the recommended biochemically verifiable window for CO in expired air [44]. The Jarvis protocol will be used to record expired air CO. A cut-off point of 8 ppm will be used to define a smoker [44]. Measuring CO in expired air has demonstrated high sensitivity and specificity of around 90% for both [44].

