#### Efficacy of intervention

To assess the efficacy of the intervention at smoking cessation (validated by expired air CO), the intervention and control groups will be compared on each of the primary outcomes using chi-square analysis: 1) proportion abstinent last 24 hours (validated) at one, six and 12 months; and 2) proportion abstinent for seven days at one, six and 12 months. Univariate analyses will be undertaken to examine factors associated with each of the two outcomes, using the chi-square test for categorical variables and the t-test or a non-parametric equivalent for continuous variables. In addition to the primary analysis, intention-to-treat analysis will also be undertaken whereby clients who fail to complete follow-up in the study will be considered to be continuing smokers. Multiple logistic regression analyses will be used to compare outcomes between the two intervention groups while adjusting for prognostic variables and potential confounders (sociodemographic, financial stress, depression, and other variables collected).

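### Six comparisons share primary status with no lead outcome, time point or success rule, while the sample size covers one 12-month comparison at an undivided 5%

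*Protocol article*

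**What the plan says.** Under Primary outcome measure, the protocol article says: "There will be two primary outcome measures obtained at one, six and 12 month follow-up". The first outcome is CO-validated abstinence over 24 hours and the second is self-reported abstinence over seven days. Only continuous abstinence is listed as secondary.

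Under Efficacy of intervention, "the intervention and control groups will be compared on each of the primary outcomes using chi-square analysis". The two items listed there are "proportion abstinent last 24 hours (validated) at one, six and 12 months" and "proportion abstinent for seven days at one, six and 12 months". No significance level is given in that section.

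Under Sample size, "A sample of 200 participants per group at 12 months will allow detection of a difference" of 8 percentage points, "based on 5% smoking cessation in the usual care group and 13% in the intervention group", "at 5% significance level and 80% power". The same paragraph mentions a detectable difference of 7 points at 1 month. It does not say which of the two outcomes the 5% and 13% refer to.

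**The concern.** Two outcomes at three visits give six comparisons of equal standing. The article does not rank them, and does not say whether one, both or all must be significant before the intervention is called efficacious. The Study Aims section nevertheless seeks one conclusion about efficacy.

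The conclusion could therefore be chosen after the results are known. The 1-month visit shows how. With two face-to-face sessions two weeks apart and then two calls one week apart (The Case Worker Sessions), scheduled support ends at about week 4. The 1-month comparison falls near the end of that support, yet ranks equally with 12 months. A positive 24-hour result at 1 month with null results at 12 months would leave readers free to argue either way. The 5% and 80% in the sample-size section describe one test, not this family of six.

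**Working it through.** **Inputs.** From Sample size: rates 0.05 and 0.13, 200 per group at 12 months, alpha 0.05, power 0.80, 30% loss, 290 per group recruited. From Primary outcome measure and Efficacy of intervention: 2 outcomes × 3 times = 6 tests. Assumed, because the article gives none: the correlations among the six test statistics.

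**1. The plan's own figure.** With pooled variance, two-sided 5%, no continuity correction and mean rate 0.09:

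n = [1.960·√(2·0.09·0.91) + 0.8416·√(0.05·0.95 + 0.13·0.87)]² / 0.08²
= [0.7933 + 0.3373]² / 0.0064 = 199.7, so 200 per group.

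This matches the article. A one-sided test would need 158 and a continuity-corrected two-sided test 225. Allowing for loss, 200/0.70 = 286, close to the stated 290. The 1-month statement also fits: 290 × 0.90 = 261 per group gives 82% power for 5% v 12%. The size is thus that of one comparison at the full 5%.

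**2. Error rate if any one of six two-sided 5% tests counted.** Independent tests: 1 − 0.95⁶ = 26.5% in either direction, and 1 − 0.975⁶ = 14.1% in favour of the intervention. For correlated tests, six normal test statistics were simulated (500,000 draws per scenario):

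| Common correlation | Any significant result | Favouring the intervention |
|---|---|---|
| 0 | 26.5% | 14.1% |
| 0.5 | 20.8% | 10.4% |
| 0.7 | 16.4% | 8.2% |
| 0.8 | 13.9% | 6.9% |
| 0.9 | 10.7% | 5.4% |

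The single-test references are 5% and 2.5%. Setting the correlation between outcomes at 0.5-0.95 and between visits at 0.3-0.9 gives 10.7-23.8% in either direction.

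**3. If only the two 12-month tests count and either suffices.** Independent: 1 − 0.95² = 9.75%. The two-sided error is 9.1% at correlation 0.5, 7.1% at 0.9 and about 6.5% at 0.95 (bivariate normal), so about 6-10%.

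**4. If both outcomes must succeed at 12 months.** The chance of a false favourable result cannot exceed the 2.5% of a single test, so there is no inflation. If each test has 80% power, joint power lies between 0.80 × 0.80 = 64% (independent) and 80% (perfectly correlated).

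**5. Power at 200 per group if alpha is split equally.** Power = Φ[(0.08·√200 − z·0.4047)/0.4008]:
- alpha 0.05, z = 1.960: Φ(0.844) = 80.1%
- alpha 0.025, z = 2.241: Φ(0.560) = 71%
- alpha 0.05/6, z = 2.638: Φ(0.159) = 56%

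Restoring 80% would take 242 per group (346 recruited) for two tests, or 309 (442 recruited) for six. The two arms would then total 692 or 884, against the 585 consenting clients that the article expects.

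All figures treat clients as independent. Allocation by week is a separate matter and is not included.

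**The case against.** A reader might infer that this trial runs a 26% risk of wrongly calling the intervention effective. The document does not support that, for four reasons.

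- **Direction.** The 11-26% counts significant differences either way. The chance of a false finding for the intervention is about half that.
- **Correlation.** The upper end needs independent tests. The same people are followed throughout, and anyone abstinent for seven days is also abstinent for 24 hours, so 26% is a bound and not an estimate.
- **Success rule.** The article nowhere says that one significant result is enough. It does not exclude that rule either, but requiring both outcomes at 12 months would remove the inflation.
- **Level.** The 5% appears only in the sample-size section. Applying it to each chi-square test is a reasonable reading, not a stated rule.

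It can also be said that multiplicity rules commonly sit in an analysis plan, which is not shown, and that setting 200 per group at 12 months hints at a lead time point. Both are fair. The absence of an adjustment is therefore not the finding.

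What stands is what the article itself fixes: six comparisons labelled primary, and a size for one. The 12-month hint is weakened by the 1-month detectable difference in the same paragraph, and it does not choose between the two outcomes. An alpha split added later would keep the 5% but not the 80% at the stated size.

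**Conclusion.** The point holds in a limited form. Six comparisons are primary without a lead or a success rule, and the sample size supports one 12-month comparison at an undivided 5%. With the six of equal standing, a 5% error for the family and 80% power for each comparison cannot both hold at 200 per group. An equal split leaves 71% for two tests or 56% for six. These powers are per comparison; the chance that at least one of several succeeds would be higher, but the article attaches its 80% to one 12-month difference.

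If any one of six counted, the error would be about 11-26% in either direction, or about 5-14% in favour of the intervention against 2.5% for one test. If either 12-month test sufficed, it would be about 6-10% two-sided. All of these rest on assumed correlations and on a success rule that the article leaves open. The gap in the definition of the primary comparison is certain; the size of the inflation is conditional.

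**What to change.** Before results are seen, do one of the following:

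1. Name one of the two listed outcomes at 12 months as the single primary, for example 24-hour CO-validated abstinence, tested once at two-sided 5%. State that the 5% and 13% in the sample-size section refer to it.
2. Require both listed outcomes to be significant at 12 months, and restate the power for that joint requirement.

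Under either choice, make all 1- and 6-month comparisons secondary.

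A CO-verified 7-day measure may look attractive, but it is not one of the two listed primary outcomes, and the article ties CO verification to a 24-hour window. Adopting it would change the endpoint and call for a fresh justification of the assumed rates.

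The first option keeps 200 per group and 80% power, provided the assumed rates suit the chosen outcome. The second keeps the error rate, but power falls below 80% unless the two tests are perfectly correlated or the trial is enlarged. The downside of both is that an early result, including the 1-month one near the end of scheduled support, can no longer be called a primary success.
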